**Primary outcomes**				
Student observer/ PWD		INTERACT Observation Scale (Session 1 and 8)		
Independent assessor	QUALIDEM		QUALIDEM	QUALIDEM
**Secondary outcomes**				
PWD		SFAS (1^st^ and 4^th^ intervention week)		
Independent assessor	NPI-Q		NPI-Q	NPI-Q
(In)formal carer (experimental/control)	TOPICS-MDS ADQ IRI		ADQ IRI	
(In)formal carer (experimental only)			SUS	
Informal carer only	TOPICS-MDS SSCQ		SSCQ	SSCQ

The QUALIDEM specifically measures quality of life of residents with dementia living in nursing homes, as rated by formal carers. The brief Neuropsychiatric Inventory (NPI-Q) assesses mood and behaviour symptoms of the residents. The Older Persons and Informal Caregivers Survey (TOPICS-MDS) is for collecting background characteristics of residents and their (in)formal carers. The Approaches to Dementia Questionnaire (ADQ) measures person-centered attitude of (in)formal carers who provide the intervention or the control activity. The Interpersonal Reactivity Index (IRI) measures empathy. The Short Sense of Competence Questionnaire (SSCQ) measures feelings of competence of the informal carer in dealing with the PWD. The INTERACT is an observation scale used to rate the behaviour and interactions of the PWD with their (in)formal carer. The Smiley Face Expression Scale (SFAS) is a self-reported mood assessment for the PWD. The System Usability Scale (SUS) measures perceived usability

### Qualitative measures

To investigate whether informal carers feel that their role and their relationship to the person with dementia is known and acknowledged in the nursing home, the following questions in focus groups and semi-structured interviews will be asked on T0, T1, and T2:To what extent do you feel that you are known as a family/informal carer in the nursing home?How satisfied are you with the stay of your loved one in the nursing home?To what extent do you think you (or your loved one) are acknowledged in the nursing home?

To investigate the extent to which the intervention is able to strengthen relationships between the resident and their (in)formal carers, the (in)formal carers who deliver the Photo-Activity intervention or the control activity will be asked the following in focus groups and semi-structured interviews at T1:To what extent did you get to know the resident and his or her family member better as a result of the Photo-Activity intervention/ general conversation activity?

Finally, a process evaluation, via semi-structured interviews with the (in)formal carers and residents, will be done to evaluate the experiences with the Photo-Activity intervention or the control activity. To inventory the factors potentially influencing the outcomes of the study, the researchers will use a pre-determined list of questions based on the Medical Research Council (MRC) guidance for process evaluation of complex interventions [77], where contextual and implementation factors and impact mechanisms (learnability, user-friendliness, usability and adoption) are explored as factors that may have an influence on the intervention outcomes.

Analytics data are also collected from the Photo-Activity web-app (called the *Fotoscope),* via Google Analytics to be able to assess how the web-app was used. Users are given unique usernames that are distinct from their participant code in the study, so that data from Google Analytics is not identifiable, except for members of the main research team who holds the key to the codes.

Two focus groups, based on purposive sampling, will also be held as part of the process evaluation of Phase II, involving residents with a diverse background in terms of age, gender, cultural background, and severity of dementia, together with the residents’ loved ones, (in)formal carers, and the ward managers (stakeholders). Three to eight participants per group will be formed in order to give the participants more chances to contribute to the conversation [78]. The focus groups, led by a moderator and observer, will be conducted face-to-face, or via online video-calls, depending on the current government COVID-19 restrictions.

In Phase III, the implementation toolkit will be compiled to promote sustainable implementation, dissemination, scaling up and assurance of knowledge. The toolkit will consist of the Photo-Activity app, and a digital implementation guide (fact sheet) for the management of care institutions, validated by a panel of care providers, PWD, family members, teachers (MBO and HBO), managers and researchers.

### Data collection procedure

Recruitment period and data collection is currently on-going, starting from February 2021 to June 2022.

### Quantitative data

One staff-member from the ward is assigned the role of the *coordinator*, who becomes the primary contact of the researchers in terms of recruiting residents and their families, and collecting informed consents. The coordinator sends out the project invitation along with the informed consent forms to the families of the residents. Once the coordinator gains the informed consent of the resident (where possible) and their legal representative, the researchers then contact and start collection of demographics and baseline information via sending online questionnaires to the (in)formal carers. The online questionnaires include outcome measures mentioned above. All questionnaires are sent at T0, T1 and T2, except for the demographic/background questionnaires which are only sent at T0, and for the questionnaires specifically for (in)formal carers delivering the intervention or control activity which are sent at T0 and T1 only.

Medical information such as type of dementia, severity of dementia, and information on medication related to dementia are collected by the researcher from the coordinator at T0. Medication information is again collected at T1 and T2.

The (in)formal *carers delivering the interventions* (either the Photo-Activity or General Conversation activity) are asked to keep a record of session details, including date and time, duration, and reason if a session is missed. The (in)formal carers also collect information about the resident’s mood before and after a session, using the SFAS [79]. This is done at the first and last week of the intervention period (in total, data on residents’ mood is collected 4x2 times).

The formal carers acting as *Independent Assessors* receive training on how to assess the resident, and based on their observations, to fill out the QUALIDEM [61], the NPI-Q [67], and to ask the residents a couple of questions from TOPICS-MDS [60] about their health and life satisfaction, and questions about feeling known in the nursing home, and levels of satisfaction with their stay in the nursing home. Independent Assessors are also asked to note down any significant events in the resident’s life (for example, when a resident becomes ill), during the intervention period. These data are collected through online questionnaires and are done at T0, T1 and T2.

Data on residents’ positive emotions and social interactions with their (in)formal carers will be collected by trained students or interns using the INTERACT scale [56]. They will be present to observe the first and last Photo-Activity or General Conversation activity via online video-calls, keeping in line with the Covid-19 restrictions.

### Qualitative data

#### Phase II

At the end of the four-week intervention period, a process evaluation is conducted by asking the residents and their (in)formal carers about their experiences in being part of the Photo-Activity or the General Conversation Activity, as described above. The residents are interviewed by the student observer during their last session, via online video-call. The (in)formal carers are given the option of completing the list of questions on their own time, or answering the questions via phone-conversation with the student observer.

#### Phase III

Two focus groups, one from each participating care organization, will also be held to validate the implementation toolkit, as described above. Approximately 1.5 hours in length, the discussions will involve the functionality and design of the draft toolkit, keeping in mind ways to adapt the mode of instruction to different target groups.

### Data management and monitoring

The researcher contacts (in)formal carers at the start of the project (after gaining informed consent), and follows-up with data collection during the entire period. The researcher encourages the (in)formal carers to ask questions and to contact the research team for any comments or feedback. Upon recruitment, residents and their (in)formal carers are informed that personal data are collected and will be treated as confidential, i.e. all data will be anonymized and linked to a unique participant code and saved in a secured and privacy protected database. The key to the code that links to their personal data is only accessible to the research team and will be destroyed after the end of the project. Usernames for residents and (in)formal carers to access the digital Photo-Activity app are given another separate and unique, random code, of which the key linking the app usernames to the participant personal data codes is again only accessible by the members of the research team.

The research data cannot be traced back to the individuals in case of publication of research results in any journal or publication. Signing the consent forms will imply that participants consent to the researchers collecting, storing, and accessing their personal data, and that these data will be kept for 10 years after the end of the study period. Participants are informed that they are free to withdraw themselves and their personal data from the study at any time. Participants are also asked if they consent to their coded data being added to a national database that will be made available for new studies.

Personal and quantitative trial data will be collected and stored online, via Castor Electronic Data Capture (Castor EDC), a cloud-based clinical management platform [80], that complies with the Good Clinical Practice (GCP) laws and regulations. Data in Castor is regularly backed-up, retrievable, and trackable with an audit trail in Castor EDC’s secure servers based in the European Union. Access to the database is protected by a password and the use of two-factor authentication. Each Castor user is assigned a role that determines the level of access they have to the data.

For data that needs to be collected in paper form and sent via email from the nursing homes, researchers will request the nursing home staff to send these documents via Zivver [81], which is a platform that allows secure sending of sensitive information and files via email. Once received by the researcher, names of participants are removed and the files are coded, saved, and stored in the secure, password-protected, digital workspace used by the Department of Psychiatry within the mental health organization GGZ inGeest.

Original and printed documents are also anonymized, coded, and stored securely in a locked office. Informed consent forms are stored in a locked drawer to which only the research team has access. Any copies containing personal information are disposed of via a secure and confidential document disposal service.

The researcher monitors and keeps track of the progress of data collection, following-up missing data or addressing data discrepancies, via the reminder function in Castor, email communication or follow-up phone calls with the participants.

The project has been assessed scientifically and is embedded within the Amsterdam Public Health (APH) research institute, which holds regular sample audits, therefore a data monitoring committee is not needed. The researcher ensures that the project is in line with the guidelines set by the APH research institute [82].

A Data Management Plan for the collection, management, analysis and storage of the data will be created in line with Open Science, and based on the principles of FAIR data (Findable, Accessible, Interoperable, and Reusable). Data from the survey will be made available to the TOPICS-MDS, a public data repository in the Netherlands [83].

## Analysis

### Quantitative data

Analysis for quantitative data will be done using SPSS for Windows. Participant characteristics are analyzed with descriptive statistics and differences are tested with parametric or non-parametric tests dependent on type of data. Multilevel analysis (MLA) is performed to investigate whether the averages on continuous outcome measures at T1 and T2 differ between experimental and control groups. Baseline measurements (T0), severity of dementia and potential confounders are included in the analyses as covariates. The MLA takes into account the clustering of people with dementia and caregivers within nursing wards. The same procedure is used for dichotomous data, but the analyses are then performed with General Estimations Equations. Both intention-to-treat and ‘per protocol’ analyses will be done.

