### Quantitative measures

#### Primary outcomes

For the residents, positive emotions and social interaction with their (in)formal caregiver during the activity session are assessed by trained students with the INTERACT observation scale [56] during the first and last intervention session.

Quality of life is evaluated by formal carers who are assigned the role of Independent Assessors, with the QUALIDEM [61] based on their observations of the behaviour of the resident in the previous week at T0, T1, and T2. These formal carers are trained in the use of the instrument by a member of the research team. The QUALIDEM was developed specifically to measure quality of life of residents with dementia living in nursing homes, as rated by the formal carers. It is made up of 37 items that describe behaviour that can be observed by the carer. Carers can choose from the answer options of ‘never, seldom, sometimes, and often [62]. The QUALIDEM has been found to have sufficient reliability and validity, and is an easy questionnaire to administer [61, 62].

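### The one stated model for continuous outcomes (T1 and T2, adjusted for T0) cannot be run on the primary outcome INTERACT, which is rated only during sessions 1 and 8 of the allocated activity

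*Protocol article*

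**What the plan says.** The Analysis section (Quantitative data) states one procedure for every continuous outcome. The comparison is "Multilevel analysis (MLA) is performed to investigate whether the averages on continuous outcome measures at T1 and T2 differ between experimental and control groups". On covariates it adds: "Baseline measurements (T0), severity of dementia and potential confounders are included in the analyses as covariates". The Methods/Design section defines T0 as baseline, T1 as the end of the four-week intervention and T2 as two weeks later.

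The schedule for INTERACT differs. Under Primary outcomes, positive emotions and social interaction "are assessed by trained students with the INTERACT observation scale [56] during the first and last intervention session". Table 1 lists "INTERACT Observation Scale (Session 1 and 8") in the column for the intervention period and leaves the T0, T1 and T2 columns empty for this scale. The data collection section says of the student observers: "They will be present to observe the first and last Photo-Activity or General Conversation activity via online video-calls". Both ratings are therefore made while the photo sessions or the control conversations are under way.

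QUALIDEM, the other primary outcome, is scheduled at T0, T1 and T2. SFAS, a secondary outcome, is rated before and after sessions: "This is done at the first and last week of the intervention period".

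The sample size paragraph rests on pilot INTERACT effects (d = 0.86 and 0.85) that were observed during the intervention.

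**The concern.** The analysis rule needs a T0 value to adjust for and T1 and T2 values to compare. INTERACT supplies none of these, so a primary outcome, and the one used for sizing, is left without a model that can be executed as written.

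The nearest adaptation is to let session 1 stand in for T0 and session 8 for T1. Session 1 takes place after randomisation, after training that differs between arms, and with the allocated activity in progress. Because the pilot effects were seen during the activity, some effect may already be present at session 1. An adjusted comparison would then subtract part of the effect it is meant to estimate. Leaving the choice open also means it could be made after the data have been seen.

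**Working it through.** **1. Schedule against model.**

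| Outcome | T0 | T1 | T2 | Stated rule usable? |
|---|---|---|---|---|
| QUALIDEM (primary) | yes | yes | yes | yes |
| INTERACT (primary) | no | no | no | no: sessions 1 and 8 only |
| SFAS (secondary) | no | no | no | not as labelled, but a rating before session 1 exists |

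**2. The plan's own figure.** The inputs are power 0.80, α = 0.05, d = 0.8 and 10% dropout, and the stated result is 45 per group. A two-sided t-test with these inputs needs 26 per group, and 26/0.9 = 28.9, so 29 with dropout. The 45 is not reproduced. That is a separate matter and does not affect this point. For what follows, 45 × 0.9 = 40.5 completers per arm, taken as 40.

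**3. Reference power.** An unadjusted comparison at session 8 with d8 = 0.8 and 40 per arm has noncentrality 0.8 × √(40/2) = 3.58. Power is 94% (two-sided 0.05, noncentral t, clustering ignored).

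**4. Effect of adjusting for session 1.** Take SD = 1 at both sessions, within-arm correlation r, and effects d1 and d8. A regression of session 8 on arm and session 1 has

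- expected arm coefficient: d8 − r·d1
- residual SD: √(1 − r²)
- standardised effect: (d8 − r·d1)/√(1 − r²)

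The documents give neither d1 nor r, so both are assumed. With d8 = 0.8 and 40 per arm:

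| d1 | r | coefficient | share kept | standardised | power |
|---|---|---|---|---|---|
| 0 | 0.3 / 0.5 / 0.7 | 0.80 / 0.80 / 0.80 | 100% throughout | 0.839 / 0.924 / 1.120 | 96% / 98% / over 99% |
| 0.4 | 0.3 / 0.5 / 0.7 | 0.68 / 0.60 / 0.52 | 85% / 75% / 65% | 0.713 / 0.693 / 0.728 | 88% / 86% / about 90% |
| 0.8 | 0.3 / 0.5 / 0.7 | 0.56 / 0.40 / 0.24 | 70% / 50% / 30% | 0.587 / 0.462 / 0.336 | 74% / 53% / 32% |

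A simulation of the case d1 = 0.8, r = 0.5 gave a mean coefficient of 0.40, which agrees with the formula. The power figures leave out ward clustering. They also leave out the extra standard error that arises when the covariate itself differs between arms, so the rows with d1 above zero are slightly optimistic.

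**5. Reading the table.** The loss is r·d1. It is zero when session 1 carries no effect, and in that case adjustment gains precision. The loss becomes serious only when most of the effect is already present at session 1 and the sessions are strongly correlated.

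**The case against.** The strongest reply is that the document never states the harmful analysis. Adjustment is restricted to T0 values, and Table 1 keeps INTERACT out of the T0 column. Read literally, there is no INTERACT baseline to adjust for, and the same multilevel model could be run on session 8 with severity of dementia and no session-1 term. Outcome-specific models are also commonly left to an analysis plan. This stands in part. A reader might infer that the trial will adjust away its own treatment effect, or that using session 1 as baseline is the only way to apply the rule. The text supports neither. What remains is that the article does state a rule for all continuous outcomes, and that its own schedule makes the rule inapplicable to a primary outcome.

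A reader might also infer that most of the power would be lost. That holds only if the full effect is present at session 1 and r is high (32% at r = 0.7). With half the effect at session 1, power stays at about 86–90%. An effect seen during the pilot sessions makes an early effect plausible, but it does not show that the session-1 effect equals the session-8 effect.

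Two neighbouring points do not hold as errors. The text says "with the INTERACT observation scale [56] during the first and last intervention session" where Table 1 says session 8. Two sessions a week for four weeks make eight, so the planned last session is session 8. SFAS does not share the full problem either, because a rating before session 1 is collected. It needs only to be named as the baseline.

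**Conclusion.** The mismatch is established from the text alone: the stated model cannot be run on INTERACT, and the article does not say what replaces it. QUALIDEM is unaffected. The bias is conditional on session 1 being used as baseline, which the document does not say. In that case the expected effect is d8 − r·d1. The range runs from no loss to 70% of the effect over the assumed values (d8 = 0.8, d1 from 0 to 0.8, r from 0.3 to 0.7, 40 per arm, equal SDs, no clustering). Because this is a primary outcome and the one the trial was sized on, the ambiguity should be closed before any INTERACT data are compared by arm.

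**What to change.** In the Analysis section, add a separate INTERACT model:

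- Sessions 1 and 8 both enter as outcomes in the multilevel model, with arm, session and arm-by-session terms, repeated measures within resident, and clustering by ward.
- Covariates are pre-randomisation only: severity of dementia and provider type. State that session-1 INTERACT is never a covariate.
- The single primary contrast is the arm difference at session 8. The session-1 difference is reported as supportive.

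For SFAS, state that only the rating before session 1 serves as baseline and that later ratings are outcomes.

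The cost is a paragraph of text and slightly more analysis work, with no new data. With complete data the session-8 contrast keeps roughly the unadjusted power of 94% at d = 0.8 before clustering. It forgoes the precision that adjusting for session 1 would bring if session 1 in fact carried no effect.

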**Fig. 1 Fig1:**
[figure not shown]
Description of one cycle involving a PWD and their (in)formal carer

The groups will be stratified on severity of dementia, based on a Global Deterioration Scale (GDS) [54] score of 4 to 6, the person doing the intervention (informal carer who can be a family member or relative; or a formal carer), and nursing home. Residents will be randomized after stratification. Allocation of residents with dementia and (in)formal carers to the experimental or control group will be done via manual drawing of lots by the researchers, and (in)formal carers are informed of the assignments afterwards.

In addition, effects of the experimental intervention versus the control intervention in informal carers will be investigated regarding their feelings of competence. Effects on the (in)formal carers who provide the Photo-Activity intervention (experimental group) or the general conversation sessions (control group) with the residents, are compared regarding attitude and empathy in both groups.

During the trial period, a process evaluation will also be conducted where residents and their (in)formal carers at the end of the 4-week intervention will be asked about their experiences with the implementation of the Photo-Activity intervention, in order to gain insight into factors that may have influenced the study outcomes, such as the user-friendliness and usability of the Photo-Activity app, the frequency of use, and facilitating and impeding factors towards successfully implementing the Photo-Activity intervention. Residents who participated in the general conversation activity and the (in)formal carers who delivered this activity will also be asked about their experiences.

In Phase III, based on the results of the process evaluation, an implementation toolkit will be developed as described in the Objectives.

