### Study setting and participants

The study will be conducted in 14 nursing home wards that are part of 2 large care organizations in the Netherlands (in the Amsterdam and Haarlem region). PWD in these participating nursing home wards who meet the inclusion and exclusion criteria (regardless of gender, age, socioeconomic status, and ethnicity), along with their legal guardians, will receive a written invitation from the nursing home with a consent form for participation and information about the study.

Based on the pilot study with the Photo-Activity, in which large positive effect sizes were found for social interaction (d= 0.86) and reduced negative behaviour (*d*=0.85) using the INTERACT scale [55] during the intervention [35], a power-analysis (power 0.80, α=0.05, *d*=0.8) and expected 10% dropout in 6 weeks, for this explorative study 45 people with dementia are needed per group (total of 90) to find statistically significant large effects. The researchers will promote the project in the care organizations and work with the research coordinators, ward managers and team leaders in order to meet the required recruitment target.

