### Eligibility criteria

#### Inclusion criteria

Residents with dementia (Alzheimer’s disease, vascular dementia, Mixed Alzheimer’s-vascular dementia, front-temporal dementia, Lewy Body disease, or others) whose score range from 4-6 (moderate to severe dementia) on the GDS [54], and have been admitted to the nursing home for at least 1 month are eligible for the study. Those who give their consent and who agree to participate will be included, and after stratification (severity of dementia; intervention provider; and nursing home), will be randomly assigned to an experimental or control group. Formal carers will also be randomly assigned to deliver the experimental or control activity.

For the informal carers, they will be assigned to the same activity where their loved one is randomly assigned to, and there are no specific inclusion criteria, except that they are willing to participate in the study themselves as well as to provide information on the interests of their loved one. If they would like to be involved in carrying out the Photo-Activity or control intervention for their loved one, they additionally must be willing to participate in a short training to deliver the intervention and be able to commit to providing the intervention for 2 half hour sessions a week, for a period of 1 month.

The formal carers of the included PWD’s are invited and trained to deliver the experimental/control intervention and to be a part of the study after providing informed consent. The recruitment of formal carers will focus on those who work enough hours to fulfill the criteria of delivering the experimental or control activity twice a week for 4 weeks. Information about characteristics of the formal carers delivering the intervention (work function, training level, experience, working hours, etc.) will be collected.

For formal carers assigned to be Independent Assessors, i.e. not involved in the interventions, recruitment criteria are that they are present in the ward for more than 2 days a week, and have regular contact with the residents. The Independent Assessors are asked to complete outcome measures about the residents. Because no information is collected on the Independent Assessors themselves, they are not asked to fill out the consent forms.

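### Intervention provider (informal or formal carer) is a stratification factor but is not named in the analysis model; naming it is a nearly free gain, mainly for INTERACT

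*Protocol article*

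**What the plan says.** Two places in the protocol article give the same three stratification factors. Methods/Design, in the text after Fig. 1, lists dementia severity on the Global Deterioration Scale, then "the person doing the intervention (informal carer who can be a family member or relative; or a formal carer), and nursing home". Inclusion criteria repeats that residents, "after stratification (severity of dementia; intervention provider; and nursing home), will be randomly assigned to an experimental or control group".

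Analysis, Quantitative data, describes a multilevel model for continuous outcomes and gives its covariates: "Baseline measurements (T0), severity of dementia and potential confounders are included in the analyses as covariates". On clustering it says: "The MLA takes into account the clustering of people with dementia and caregivers within nursing wards". Provider type is not named there.

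Under Primary outcomes and in Table 1, INTERACT is scored by student observers at sessions 1 and 8 only. QUALIDEM is rated by Independent Assessors at T0, T1 and T2.

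**The concern.** A trial should normally be analysed with the factors it used to balance the arms. Stratifying on a prognostic factor removes its contribution to the chance difference between arms. A model that leaves the factor out does not know this and keeps that variance in the residual. The reported standard error is then larger than the true one, the test rejects too rarely under the null, and part of what stratification gained is lost.

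The primary INTERACT outcome is where this could show. It scores the resident's emotions and social interaction with the person running the session, so whether that person is a relative or a staff member is part of what is observed. Both observations fall within the intervention period, so there is no T0 value to absorb a provider-related difference. Of the covariates the article names, only severity remains for this outcome.

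**Working it through.** **Design factors against model terms**

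| Stratification factor | Stated place in the model |
|---|---|
| Severity of dementia | Named covariate |
| Nursing home | Largely covered by ward clustering (taking wards as nested in homes) |
| Intervention provider | None named |

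**The plan's own sample size.** Study setting and participants gives "a power-analysis (power 0.80, α=0.05, *d*=0.8) and expected 10% dropout in 6 weeks" and concludes that "45 people with dementia are needed per group (total of 90) to find statistically significant large effects". With those inputs, two-sided, n = 2(1.96 + 0.84)²/0.8² = 24.5, so 25 per arm (26 by the t-test). Dividing by 0.9 for dropout gives 28 to 29. The stated 45 is not reproduced. That is a separate matter and does not affect this point. I take the stated 45 and its 10% dropout: 45 × 0.9 = 40.5, so 40 evaluable residents per arm.

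**Inputs for the effect of leaving provider type out**
- 40 per arm and outcome SD 1, so SE₀ = √(2/40) = 0.2236.
- R², the share of outcome variance explained by provider type beyond the other covariates. The documents give no value. Assumed range: 0.01 to 0.20.
- Provider type balanced across arms by the stratification.
- Ward clustering is ignored here, for simplicity.

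**Formulas**
- SE ratio, without against with the factor: 1/√(1 − R²)
- True two-sided type I error without it: 2[1 − Φ(1.96/√(1 − R²))]
- Power with it: Φ(d/(SE₀√(1 − R²)) − 1.96)
- Power without it, factor exactly balanced: Φ((d/SE₀ − 1.96)/√(1 − R²))

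| R² | SE ratio | Type I error without | Power at d = 0.8, without → with | Power at d = 0.6, without → with |
|---|---|---|---|---|
| 0.01 | 1.005 | 0.049 | 0.948 → 0.949 | 0.766 → 0.769 |
| 0.05 | 1.026 | 0.044 | 0.952 → 0.956 | 0.771 → 0.786 |
| 0.10 | 1.054 | 0.039 | 0.956 → 0.965 | 0.777 → 0.807 |
| 0.20 | 1.118 | 0.028 | 0.965 → 0.979 | 0.791 → 0.851 |

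If the drawing of lots balances provider type no better than chance, the test without it keeps about its nominal size. Its power is then Φ(d/SE₀ − 1.96): 0.947 at d = 0.8 and 0.765 at d = 0.6. The powers with the factor stay about as in the table. The gain from naming it is then slightly larger, but the test without it is no longer conservative.

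**What such an R² means.** If provider type shifts the outcome by δ within-group SDs and a share p of residents has an informal provider, R² = p(1 − p)δ²/(1 + p(1 − p)δ²). With p = 0.5, δ = 0.4 gives 3.8% and δ = 0.8 gives 13.8%. With p = 0.2, the same shifts give 2.5% and 9.3%. Both p and δ are assumptions. Informal delivery is optional in Inclusion criteria, so the split cannot be known in advance.

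**The case against.** **The covariate list is open-ended.** It ends with unnamed possible confounders, and provider type may be among them. This stands: the exact statement is that the article does not name provider type, not that the model omits it. But severity, a factor of the same standing, is named, so provider type should be too.

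**The loss is small and in the safe direction.** This also stands. Nothing is biased, the test is at worst conservative, the article calls the study explorative, and power at the planned d = 0.8 barely moves.

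**It hardly touches QUALIDEM.** Largely true. QUALIDEM is rated outside the sessions by other staff and has a T0 value, which would absorb much of any stable provider-related difference. The point rests mainly on INTERACT.

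**Balance is not assured.** Lots are drawn by hand and no blocking is described, so the achieved balance is unknown. The type I figures apply only to the balanced case.

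**A stronger reading.** A reader might infer that adjustment will be data-driven, because the same section says of participant characteristics that "differences are tested with parametric or non-parametric tests dependent on type of data" and then leaves the confounders unlisted. The documents do not support this. Nowhere do they say that those tests select covariates. A covariate list is detail that a condensed article may leave to an analysis plan. In a simulation with four candidate covariates and 40 residents per arm, selecting covariates by baseline tests kept type I error at 0.038 to 0.044. It rose to 0.08 to 0.12 only when the most favourable of all covariate subsets was picked, which the article does not plan.

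**Conclusion.** The point holds in a narrow form. Randomisation uses three factors, and the stated model visibly accommodates two of them. Provider type has no named place. If it is prognostic and balanced, a model without it has a standard error about 0.5% to 12% too large for an assumed R² of 0.01 to 0.20. A nominal 5% test then runs at about 4.9% down to 2.8%. At d = 0.8 the largest power difference in the balanced case is 0.965 against 0.979. At d = 0.6 it is 0.791 against 0.851.

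These sizes depend on an R² that the documents do not supply. If provider type does not predict the outcome, nothing is lost. The case is best for INTERACT and weak for QUALIDEM. This is a worthwhile improvement at almost no cost, not a threat to the validity of the trial. The unlisted confounders and the baseline significance tests form no part of the conclusion.

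**What to change.** In Analysis, Quantitative data, add provider type (informal or formal carer) to the named covariates. The model would then carry severity of dementia, provider type and, where one exists, the T0 value of the outcome as fixed covariates, with ward kept as the cluster. For INTERACT, which has no T0 value, it would carry severity and provider type.

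The cost is a few words in one sentence and one degree of freedom. Provider type must already be known for each resident in order to stratify, so no data are added and the sample size does not change.
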